**Data monitoring and quality control**

Data on all thrombolytic patients in both the PEITEM and control group will be recorded in a secure, purpose-built web-based data entry system. The system provides pre-defined logic checks to identify erroneous, illogical data entries. All patient data will be de-identified and entered by a local trained study-specific delegate who is independent from the study team at each participating hospital. The database is only accessible via a secure login system and only accessible to those approved to do so. Moreover, only the de-identified documents are preserved and monitored by an independent contract research organization throughout the study period. All recruitment will be checked by research specialists from an independent contract research organization (CRO) throughout the study period. Finally, a data quality meeting will be held quarterly to review all the hospital records and registry data.

Data will include the detailed eligibility assessment and demographics, National Institutes of Health Stroke Scale (NIHSS) score, prestroke modified Rankin Scale (mRS) score, risk factors, hemorrhagic transformation, baseline blood pressure, prior antiplatelet usage, DNT, onset-to-needle time (ONT), modified Rankin Scale (mRS) score at discharge and 90 days. mRS score at 90 days of AIS patients will be followed up with telephone questionnaires by external clinical evaluators who are blinded to the patients’ clinical data.

**Trial management and monitoring**

The Trial Management Group (TMG) will be responsible for all aspects of local organization and the day-to-day running of the trial, including monitoring outcome data collection, and ensuring the implementation of PEITEM intervention to the participating hospitals. An independent Trial Steering Committee (TSC) will oversee the trial, and they will meet at least monthly to consider and address strategic issues. Moreover, a training physician from the department of neurology in each cluster will act as a quality coordinator. The quality coordinator’s role includes interacting with physicians once gaps in the PEITEM intervention are identified, identifying barriers for the implementation and ensuring that all the intervention are implemented. There will be a run-in period before the start of the trial. The TMG will have regular meetings with quality coordinators of the PEITEM hospitals to discuss the detail of the video conferences and to assess the infrastructures to ensure that the intervention programs can be carried out regularly after the trial begins. The evaluation of outcome will start after the run-in period. The member of a Data Monitoring Committee (DMC) will act independently of the TSC, TMG and funder, will monitor data, check the data quality submitted by the study-specific delegate, and make recommendations to the TSC on whether there are any ethical or safety reasons, if exist, why the trial should not continue. Deaths by any cause in the 1 year after hospitalization, the Serious Adverse Events (SAEs), will be recorded and reported in this trial. The DMC will monitor the occurrence of SAEs.

**Intervention**

Hospitals assigned to the PEITEM group will implement the PEITEM intervention from January 1, 2019 through December 31, 2019. The PEITEM intervention components are grounded in the behavioral theory in the Behavior Change Wheel (BCW) method.^17^ The BCW emphasizes the importance of ensuring that proponents have the capability, opportunity and motivation to perform the desired behavior through nine interventions. The PEITEM intervention will implement six of them including **P**ersuasion, **E**nvironmental reconstruction, **I**ncentivization, **T**raining, **E**ducation and **M**odeling.

*Persuasion and Modeling* aim to foster communication between clinicians and research team to stimulate clinician’s action to shorten DNT and to provide a good example to follow. A series of measures are embedded such as setting up DNT target, time tracking with feedback, case discussion and championship experience presentation to decrease in-hospital delay. *Training and Education* can help to improve the skills and knowledge of the clinicians. The Education involve the early identification of eligible patients for IVT, rapid decision-making based on the rapid risk evaluation of hemorrhagic transformation and complication management, and the training of sustainable application of quality improvement tools; the purpose will be to help rapid diagnosis, decrease initial refusal and improve complication management. *Incentivization* encouraged stroke doctors to create expectation of reward. We will establish a pioneer award according to the number of IVT patients and the proportion of DNT ≤ 60min. Finally, we will implement the standardized medical record templates involving evidence-based performance measures to indicate *Environment reconstruction*, as a persist intervention, aiming to change the physical context of patients’ information collection. A summary of the PEITEM intervention and its link with the BCW is shown in **Fig B** and a detailed description is given in **Table A.**

The PEITEM intervention will be implemented by a professional medical quality care initiative (QCI) team. Stroke team and emergency department team of intervention group will attend a 2-hour video tele-conference monthly. Training video or slides will be provided to the clinicians who can not attend the video tele-conference on time. Each hospital in the intervention group will provide formal documentation of completed training such as photos and attendance logs to guarantee adequate knowledge translation on the implementation of each intervention to the QCI team.

**Outcomes**

The primary outcome is the proportion of DNT ≤ 60 min in the AIS treated with IVT, indicating a fast thrombolytic treatment from hospital arrival. The secondary outcomes include the key time intervals between assessment and thrombolytic treatment (median DNT, ONT), mRS score and death at discharge, complications after IVT [symptomatic intracranial hemorrhage (sICH)] and favorable functional outcomes (score of 0 to 1 on the mRS at 90 days), which indicate the efficiency and safety of PEITEM intervention. The DNT is defined as the time between hospital arrival and the initiation of IVT. The ONT is defined as the time between the symptom onset and the initiation of IVT. sICH is defined as intracranial hemorrhage at 24 hours associated with an increase of ≥4 points of NIHSS score from baseline, according to European Cooperative Acute Stroke Study (ECASS) II trial.^18^

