**Participants: study clusters and their patients**

In China, hospitals are classified into 3 grades: community hospitals are defined as primary grade, hospitals that serve several communities are defined as secondary

grade, and central hospitals for a certain district or city are defined as tertiary grade. Only secondary or tertiary public hospitals with emergency departments (EDs) and neurological wards that admit patients with stroke and had the capacity to administer intravenous rtPA were eligible to participate in this trial. Hospitals participating in the Zhejiang Stroke Alliance meeting the inclusion and exclusion criteria are eligible for inclusion in the MISSION trial. Hospitals meeting the following criteria are eligible for the study: (1) agree to participate in the ongoing data report and continuous audit of IVT processes of care and outcomes; (2) have a stroke unit or staffing equivalent to a stroke physician and a nurse. The hospitals with fewer than 20 thrombolytic cases per year will be excluded. Only the AIS patients receiving IVT within 4.5 hours are eligible for inclusion.

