**Clusters randomization and blinding**

Because the hospitals are the intervention targets, they are used as the randomization unit to minimize contamination. The hospitals will be stratifically randomized with a 1:1 allocation ratio according to their baseline proportion of IVT patients with DNT ≤60 minutes (<60%, ≥ 60% -≤ 72%, >72%) collected in the pre-intervention period. The randomization will be conducted by using a computer generated randomisation sequence, by which eleven hospitals are assigned to the intervention group and another eleven hospitals to the control group. Masking the hospital personnel and clinical investigators to site or group assignment is not possible because of the intervention nature. Nevertheless, external clinical evaluators assigned to assess the outcomes will be masked.

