**Statistical Analysis Plan**

We will use the intention-to-treat analysis to analyze all outcomes. The baseline characteristics of hospitals and patients will be analyzed between the PEITEM and control groups. We will summarize continuous variables as median with interquartile ranges and categorical variables as frequency and percentage, and analyze them by using Wilcoxon rank-sum test and Chi-square test separately. Modes will be used to impute missing values of categorical variables, and medians will be imputed for missing values of continuous variables.

Intra-cluster correlation coefficients (ICC) will be calculated using the correlation-based estimation methods for categorical outcomes and analysis of variance methods for continuous variables, respectively.^19^ Generalized estimating equation models with an exchangeable working correlation structure will be conducted to account for the correlations of observations within clusters (hospitals).^20^ Odds ratios for the binary outcomes (DNT ≤ 60 minutes, sICH, favorable functional outcome at 90 days, and death at discharge) and mean differences for the continuous outcomes (DNT, ONT, and mRS score at discharge) will be estimated to assess the treatment effects. Multivariable model for DNT ≤ 60 minutes, DNT, and ONT will be adjusted for patient characteristics (including age, sex, history of stroke/TIA, hypertension, diabetes, atrial fibrillation, coronary heart disease, prior antiplatelet usage, thrombectomy, smoking, prestroke mRS score, and NIHSS score at admission) and hospital characteristics (including hospital grade [tertiary and secondary], stroke unit, teaching hospital status, and annual stroke discharge). Clinical outcomes will be adjusted for age, pre-stroke mRS score, NIHSS score at admission, and other patient characteristics with a p value of <0.1 in the univariate analysis.

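### The primary outcome counts only IVT-treated patients, a group that PEITEM itself can change, and no listed outcome shows whether it did

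*Protocol*

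**What the plan says.** Hospitals are randomised, and patients enter later, through treatment: "Only the AIS patients receiving IVT within 4.5 hours are eligible for inclusion" (Participants). The primary outcome has the same denominator: "The primary outcome is the proportion of DNT ≤ 60 min in the AIS treated with IVT" (Outcomes). The people who decide on treatment know their arm: "Masking the hospital personnel and clinical investigators to site or group assignment is not possible because of the intervention nature" (Clusters randomization and blinding).

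The Intervention section describes three PEITEM elements that bear on this denominator:

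- The incentive: "We will establish a pioneer award according to the number of IVT patients and the proportion of DNT ≤ 60min".
- The teaching: "The Education involve the early identification of eligible patients for IVT".
- Its aim: "the purpose will be to help rapid diagnosis, decrease initial refusal and improve complication management".

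Control hospitals receive routine care plus the registry (Design).

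The analysis section says: "We will use the intention-to-treat analysis to analyze all outcomes". It also compares patient characteristics between arms and adjusts the model for the primary outcome for twelve patient variables and four hospital variables. The data section covers all thrombolysed patients in both arms, with recruitment checked by an independent contract research organisation. The listed outcomes are time intervals, discharge mRS, death at discharge, sICH and 90-day mRS 0 to 1. None of them measures how many patients are treated.

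**The concern.** A proportion among treated patients can change in two ways: the same patients are treated faster, or different patients are treated. Randomising hospitals makes the arriving patients comparable in expectation. It does not do so for those selected for IVT afterwards, if the intervention influences the selection. PEITEM is meant to influence it, at least in part.

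The direction is not fixed. If patients who would have been slow go untreated, the proportion rises although nobody is treated faster. If PEITEM brings in patients who would otherwise have gone untreated and who take longer to start, the proportion falls although care has improved. If it brings in straightforward, fast cases, the proportion rises. At stake is whether a positive result can be read as faster care, and whether a real gain could be partly hidden. The secondary clinical outcomes, sICH included, are measured in the same treated group.

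**Working it through.** **The plan's own figure.** Inputs from Sample size: 55% against 70%, 80% power, 5% level (two-sided, from the analysis section), ICC 0.05, 1424 patients, 22 hospitals.

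- Mean cluster size: 1424/22 = 64.7. Design effect: 1 + (64.7 − 1) × 0.05 = 4.186.
- Without clustering, 163 per arm are needed (176 with continuity correction). In total: 2 × 163 × 4.186 = 1365, or 2 × 176 × 4.186 = 1474.
- The stated 1424 lies between the two. Its power is 81.8% (normal approximation, pooled variance) or 78.5% (t with 20 degrees of freedom). No error is raised here; the figures serve only to scale what follows.

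**Shift from selection alone.** Let p be the on-time proportion without selection, f the relative change in the number treated, and q the on-time rate of the patients added or left out.

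- Patients added: p′ = (p + f·q)/(1 + f).
- Patients left out: p′ = (p − f·q)/(1 − f).

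The protocol gives p (55% in the sample-size assumption, 62% in the pre-randomisation survey). It gives neither f nor q, so both are assumptions. The table shows the shift in percentage points over both baselines.

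| Change in the treated set | q | f = 2% | f = 5% | f = 10% | f = 20% |
|---|---|---|---|---|---|
| Slow cases left out | 0–40% | +0.3 to +1.3 | +0.8 to +3.3 | +1.7 to +6.9 | +3.7 to +15.5 |
| Slow cases added | 20–40% | −0.3 to −0.8 | −0.7 to −2.0 | −1.4 to −3.8 | −2.5 to −7.0 |
| Fast cases added | 80–100% | +0.4 to +0.9 | +0.9 to +2.1 | +1.6 to +4.1 | +3.0 to +7.5 |

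The ends of the 10% range:

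- Largest: 0.62/0.90 = 0.689, a shift of +6.9. This requires every patient left out to have been late.
- Smallest: (0.55 + 0.10 × 0.40)/1.10 = 0.536, a shift of −1.4.
- If every added patient were late, 0.62/1.10 = 0.564, a shift of −5.6, which is inside the same absolute range.

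With 712 patients per arm over 11 hospitals, 10% is 71.2 patients, or about 6.5 per hospital in the intervention year. Across the clearly selective scenarios (q of 0 to 20% left out, 20 to 30% added slow, 90 to 100% added fast), a 3-point shift needs f of about 5% to 14% and a 5-point shift about 7% to 25%.

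**What a shift does to the test.** The shift is taken to occur in the PEITEM arm only. The effective size per arm is 712/4.186 = 170.1. With no true effect at 55%, the standard error is √(2 × 0.55 × 0.45/170.1) = 0.0539, so a difference of 1.96 × 0.0539 = 10.6 points reaches significance.

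- No true effect: a 3-point shift raises the two-sided rejection rate from 5% to 8.6%, and a 5-point shift to 15.3%.
- True 55% against 70%: power is about 82%. It falls to about 63% if the PEITEM rate appears as 67%, and to about 47% if it appears as 65%.

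**The case against.** The strongest reply has several parts.

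- DNT does not exist for untreated patients, the objective is confined to treated patients, and the Introduction reports earlier programmes on the same measure. This stands, and it is why the primary outcome should be kept.
- The award counts volume as well as the on-time proportion, so a hospital that leaves slow cases untreated loses on one criterion. This also stands. A reader might infer that PEITEM hospitals would raise their figure by withholding treatment; the documents do not support that as a prediction.
- Patients who first refuse and then accept are already in the denominator, and shortening that delay is a true gain in DNT. This is a fair reading of the Intervention section, which does not say that initial refusers end up untreated or that they are slow.
- A reader might take the intention-to-treat statement to be wrong because only treated patients are analysed. The protocol makes no patient-level claim: hospitals are randomised and are analysed as allocated. The statement is correct at that level; it simply does not address selection into treatment.
- Baseline comparison, covariate adjustment and the recruitment check are real safeguards. They are partial, because they describe patients who were treated and variables that were measured. They do not show how many others might have been treated, and refusal is not a covariate.
- An SAP that is not shown could add supportive analyses. However, the list of secondary outcomes is fixed in the protocol, and treatment volume is not on it even though the intervention rewards it.

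**Conclusion.** The point holds as a limit on interpretation, not as a demonstrated bias. The denominator is formed after randomisation by unmasked staff, PEITEM acts on it, and no listed outcome would reveal a difference between arms in the number treated. A 10% change in the treated set would move the primary proportion by roughly 1.4 to 6.9 points in absolute size: upward if slow cases are avoided or fast ones added, downward if slow cases are added. The upper end is a ceiling that assumes perfect selection of late patients. A 2% change moves it by about 1 point or less in nearly all scenarios.

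A reader might infer that selection could account for the whole planned 15 points. In the table only the most extreme case does so (20% of patients left out, all of them late, from 62%), and nothing in the protocol suggests a change of that kind. Both the size and the sign rest on assumed values of f and q. The change is worth making because it decides how far a result can be read as faster care.

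**What to change.** Keep the primary outcome and make three additions.

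1. Add as a secondary outcome the hospital IVT count in the intervention year, in total and split into DNT of at most 60 minutes and above 60 minutes. Compare it by arm with adjustment for the hospital's 2018 count. Report it per stroke discharge as well if discharge counts exist for each year; the protocol lists annual stroke discharge only as a hospital covariate and does not say that it is collected yearly.
2. If the counts differ by arm, add a sensitivity analysis that takes the excess or missing patients as on time or late. With an observed proportion p, removing an excess of f gives p(1 + f) − f·q, where f is relative to the expected number. Restoring a missing share f of the expected number gives p(1 − f) + f·q. For p = 70% and a 10% excess, the result runs from 0.77 − 0.10 = 67% (excess all on time) to 77% (excess all late). For 10% missing, it runs from 63% to 73%.
3. State that the primary result will be read as faster care in the light of these two analyses.

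On-time treatments per 100 stroke discharges should not become a condition for the claim. That rate rises with volume alone: per 1000 discharges, going from 100 to 120 treated at an unchanged 62% moves it from 6.2 to 7.4. If slow cases are simply avoided, its true value does not change, so its sign says little.

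The cost is a small extra analysis. The counts follow from the record of all thrombolysed patients and the 2018 pre-intervention data. The limitation is that volume is an imperfect marker of selection, and stroke discharges include patients who were never eligible for IVT.

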**Design**

The MISSION is an open label, multicenter cluster-randomised clinical trial involving 22 hospitals in China. The Zhejiang Stroke Alliance developed by Zhejiang Stroke Quality Control Center (ZSQCC) has consecutively recruited stroke patients in eastern China since 2016. This trial was approved by the human ethics committee of the Second Affiliated Hospital of Zhejiang University (SAHZU), School of Medicine. The clinical trial is conducted according to the principle expressed in the Declaration of Helsinki. Written informed consent will be obtained from the participating hospital staff. Informed consent will also be obtained from patients or their legally authorized representatives for treatment with alteplase and participation in a telephone survey at 3, 6, and 12 months after the initial stroke accordance with the local hospital standards.

The clinicians in one group of hospitals will receive the PEITEM intervention, a multi-components behavior change intervention based on the behavioral principles, as described by the Behavior Change Wheel framework, whereas the clinicians in another group of hospitals as the control will only receive routine care plus stroke registry. Study activities will be divided into two periods: the Pre-intervention (January 2018 to December 2018) and the Intervention (January 2019 to December 2019). Fig A describes the study design.

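### The only planned mortality comparison is death at discharge, so time at risk depends on length of stay; all-cause death within 90 days should be the main comparison, with its own missing-data rule.

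*Protocol*

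**What the plan says.** The Outcomes section of the protocol names "mRS score and death at discharge" among the secondary outcomes meant to show the efficiency and safety of PEITEM. The Statistical Analysis Plan section repeats this timing. Its list of binary outcomes, each to receive an odds ratio from a GEE model, ends with "favorable functional outcome at 90 days, and death at discharge". Neither section compares death at any other time, and neither sets a fixed day or a maximum stay.

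The same document plans longer follow-up:

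- Trial management and monitoring: "Deaths by any cause in the 1 year after hospitalization, the Serious Adverse Events (SAEs), will be recorded and reported in this trial".
- Design: consent covers "participation in a telephone survey at 3, 6, and 12 months after the initial stroke".
- Data monitoring and quality control: the recorded data include "modified Rankin Scale (mRS) score at discharge and 90 days".
- Outcomes: favorable functional outcome is a "score of 0 to 1 on the mRS at 90 days", which is a comparison at a fixed time.

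Two further statements bear on the analysis. Hospital grade, stroke unit, teaching status and annual stroke discharges enter only the models for DNT ≤ 60 minutes, DNT and ONT. Clinical outcomes are adjusted for patient characteristics alone. Missing categorical values are to be filled with the mode; multiple imputation appears only as a sensitivity analysis for patients lost at 90 days.

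**The concern.** Death at discharge mixes two things: how fast patients die and how long they are observed. A patient who dies the day after going home counts as a survivor, while the same patient kept two days longer counts as a death. If one arm discharges systematically earlier, it shows fewer deaths at discharge even when survival is identical.

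Such a difference is plausible here. The intervention is delivered to hospital teams who cannot be masked, and it covers complication management as well as the steps before treatment. Length of stay is not in the protocol's list of recorded data, so a shift might go unseen.

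What is at stake is the interpretation of the one formal mortality contrast in the trial, when follow-up for a fixed-time version is already planned.

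**Working it through.** **Side-by-side check.** Death is compared at discharge only. Death is recorded to 1 year, with telephone contact at 3, 6 and 12 months. mRS is recorded at discharge and at 90 days and is compared at both: as a mean score at discharge and as mRS 0-1 at 90 days. The gap is therefore specific to death; function already has a fixed-time comparison.

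**Size of the possible distortion.** The protocol states no mortality rate, length of stay or hazard, so there is no figure to reproduce. The inputs below are assumptions: 3% or 5% in-hospital death over a 10-day stay, the same constant daily hazard h in both arms, and discharge unrelated to prognosis.

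Formulas: h = −ln(1 − p)/10, and risk by discharge after a stay of L days = 1 − exp(−hL).

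| Death over 10 days | h per day | 9-day stay | 8-day stay | Shift (points) |
| --- | --- | --- | --- | --- |
| 5% | 0.00513 | 4.5% | 4.0% | 0.5 to 1.0 |
| 3% | 0.00305 | 2.7% | 2.4% | 0.3 to 0.6 |

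This is a relative reduction of about 10% for one day and 20% for two, with no difference in survival.

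On the odds-ratio scale that the plan uses, with a hazard of 0.5% per day in both arms, stays of 10 and 12 days give 1 − exp(−0.05) = 4.9% and 1 − exp(−0.06) = 5.8%, an odds ratio of 0.83. Across hazards of 0.3% to 1.0% per day, the odds ratio for 10 against 12 days stays at about 0.83. A comparison at the same fixed day gives 1.0 in every case.

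**Against sampling error.** Take the planned 1424 patients, 712 per arm, and an assumed 4% mortality. The standard error of the difference without clustering is √(2 × 0.04 × 0.96/712) = 1.04 points. With 1424/22 = 64.7 patients per hospital, the design effect is 1 + 63.7 × ICC:

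- ICC 0.01 (assumed for death): design effect 1.64, standard error 1.04 × √1.64 = 1.3 points.
- ICC 0.05 (the protocol's value for the primary outcome): design effect 4.19, standard error 1.04 × √4.19 = 2.1 points.

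A shift of 0.3-1.0 points is below one standard error in each case.

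**Effect of the imputation rule on a simple swap.** Most patients survive, so the mode of 90-day vital status is alive. Read literally, the mode rule would code every patient with unknown 90-day status as a survivor. If deaths after discharge make up a proportion d and a fraction f of them is missed, the estimate falls short by f × d. If f differs between arms, the contrast is distorted. Changing the horizon without changing this rule would exchange one problem for another.

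**The case against.** The strongest defence is that the choice is coherent. The Introduction cites in-hospital mortality and function at discharge as outcomes linked to earlier treatment, and the Outcomes and Statistical Analysis Plan sections agree with each other. In-hospital death also does not depend on telephone follow-up. That stands, and it is why death at discharge should be kept as a supporting result.

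A reader might infer more than the document supports:

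- *That the mortality comparison is biased.* The protocol states no effect of PEITEM on stay. Most of the intervention concerns time before the needle, and complication management is one education topic. An effect on stay is an inference.
- *That chance differences in stay between 11 hospitals per arm are bias.* They add to between-hospital variance, which the clustered analysis is meant to reflect. Only a systematic shift would bias the contrast. Hospital covariates in the clinical models could reduce chance imbalance but would not remove a shift caused by the intervention.
- *That function has the same defect.* It largely does not: mRS 0-1 at 90 days is already compared, with blinded telephone assessment and a multiple-imputation sensitivity analysis. Only the mean-score comparison is tied to discharge.
- *That 90-day status is available for every patient.* The plan itself expects loss to follow-up at 90 days.

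The illustration is also likely to be generous. If deaths cluster early, or the patients who leave sooner are the healthiest, fewer deaths are removed than a constant hazard implies. A shift below one standard error is unlikely by itself to decide the conclusion on death.

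**Conclusion.** The point holds for death. The sole formal mortality comparison has an observation time set by length of stay, which an unmasked hospital-level intervention could change, although follow-up that allows a fixed-time comparison is already planned. It does not show that a distortion will occur. Its size cannot be derived from the protocol; 0.3-1.0 percentage points rests on 3-5% death over 10 days, a constant hazard and a stay 1-2 days shorter in one arm, and is probably an upper illustration for that difference in stay. For mRS the point is minor. The primary outcome is not touched. This is a worthwhile, inexpensive correction to a secondary outcome.

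**What to change.** In the Outcomes and Statistical Analysis Plan sections:

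1. Make all-cause death within 90 days the main mortality comparison, analysed with the same GEE model as the other binary clinical outcomes. State the day from which the 90 days are counted.
2. Keep death at discharge as a supporting result, preferably reported with length of stay by arm.
3. Exempt 90-day vital status from mode imputation. Use multiple imputation, or analyse patients with known vital status and add a sensitivity analysis for those lost.
4. Leave mRS 0-1 at 90 days as the fixed-time functional comparison; no change is needed there.

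The cost is a few sentences and a stated missing-data rule; deaths over this period and a 3-month contact are already planned. Reporting length of stay would need discharge dates, which the protocol does not list. The downside is some loss to follow-up at 90 days, which in-hospital death avoids.
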